### Study measures

Standardized case report forms (SCRFs) developed in collaboration with Eastern Health and in consultation with other Canadian bariatric programs are used to collect relevant research and clinical data. Clinical data such as weight measures and blood work are collected by the clinical team (the nurse practitioner) and provided to the research team via a research nurse. The research nurse collects data on individual patients at each follow‐up visit using the SCRFs (Table 1).

**Table 1 Tab1:** Study measures and data collection time periods

Study Measures	Source	Variable	Time frame (s)
Socio-demographics/Lifestyle	Patient Interview	Age, sex, ethnicity, current marital status, highest level of education, occupation, current employment status, current household income level, smoking status (current, past, never)	Pre-surgery
Anthropometric	Standardized Case Report Form	Weight^1^, height^2^, BMI^3^	Pre-surgery, 3, 6, 12, 18, 24 months and annually thereafter
Medical History/Self-reported baseline comorbid conditions	Standardized Case Report Form	Diabetes, hypertension, dyslipidemia, sleep apnea, NAFLD, PCOS, etc.	Pre-surgery
Assessment of obesity-related comorbid conditions to evaluate changes in comorbid status	Standardized Case Report Form Patient Interview	Diabetes, hypertension, dyslipidemia, NAFLD, PCOS	3, 6, 12, 18, 24 months and annually thereafter PCOS will be assessed at 12 months only
Medication use	Standardized Case Report Form	Prescribed and over-the-counter medications (name, type, dosage, frequency and duration)	Pre-surgery, 3, 6, 12, 18, 24 months and annually thereafter
Clinical characteristics	Standardized Case Report Form	Blood pressure^4^, heart rate	Pre-surgery, 3, 6, 12, 18, 24 months and annually thereafter
Laboratory values	Meditech laboratory module	HbA1c, fasting blood glucose, insulin level, creatinine, fasting lipid panel (including total cholesterol, LDL, HDL, triglycerides), high sensitivity (hs) CRP, GGT, albumin, total bilirubin, ALP, ALT, total protein, ferritin, hemoglobin, MCV, TSH, 25-OH D, Vitamin B12	Pre-surgery, 3, 6, 12, 18, 24 months and annually thereafter
Health-related QoL	Validated surveys	SF 12v2, EQ‐5D, IWQoL‐Lite	Pre-surgery, 6, 12, 18, 24 months
Operative data	Clinical database and chart review	Minor and major complications	During surgery and up to 30 days post-surgery

^1^Body weight is measured using a validated, calibrated bariatric scale and recorded to the nearest 0.1 kg, with the subject wearing light indoor clothing with empty pockets, no shoes, and an empty bladder

^2^Height is measured to the nearest 0.1 cm using a wall-mounted stadiometer

^3^BMI = weight in kg/height in m^2^

^4^A single reading taking using an automated blood pressure monitor and using an appropriately sized blood pressure cuff will be recorded with the subject seated in a chair and after 5 min of rest

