#### The Newfoundland and Labrador Bariatric Surgery Cohort (BaSCo) study

##### Study objective

The objective of the current study is to examine short- to mid-term outcomes (2–4 years) associated with LSG. Eligible patients who have undergone LSG will be followed during and after surgery to assess health and other outcomes. Specific study objectives are to examine:30-day complication rate and mortality, and long-term complications (e.g., gastroesophageal reflux, micronutrient deficiencies).reduction in weight and/or body mass index (BMI), including predictors of successful weight loss.improvement or resolution of co‐morbid conditions (i.e. diabetes, hypertension, dyslipidemia, NAFLD, PCOS).changes in prescription and over-the-counter medication use.improvement in measures of health‐related quality of life andthe economic consequences associated with LSG (e.g., direct costs and indirect costs).

In the short- to mid-term we hypothesize a low rate of complications, a marked reduction in weight, improvement/resolution of comorbid conditions, a reduction in obesity-related medications, an improvement in quality of life, and a decrease in direct healthcare and indirect costs compared to pre-surgery costs.

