### Study population

#### Setting

The Provincial Bariatric Surgery Clinic is located in Eastern Health (EH). EH is the largest of four regional integrated health authorities in Newfoundland and Labrador (NL) and provides a full continuum of health services to a regional population of more than 300,000. It is also responsible for a number of unique provincial programs, for example, the Provincial Bariatric Surgery Clinic. The Provincial Bariatric Surgery Clinic was established in May 2011. This multidisciplinary team consists of three surgeons trained in bariatric surgery, a nurse practitioner, and other allied health professionals. Potential patients are most often referred via their primary care provider to the clinic and are invited to attend a pre-surgical education session. After the session, interested patients meet with the bariatric nurse practitioner where a detailed medical history is taken. Patients then meet with a bariatric surgeon, and if deemed to be a surgical candidate, they sign consent to undergo bariatric surgery, specifically LSG. At the time the team was developed, LSG was the only bariatric procedure offered to eligible patients in the province.

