#### Surgical intervention

The surgical intervention is performed laparoscopically under general anesthesia. A 6 port technique is performed. The vascular supply of the stomach is divided along the greater curve, starting 5 cm proximal to the pylorus and up to the angel of His. A gastric sleeve is created using multiple applications of a 60 mm linear stapler after the sleeve size is calibrated using a 42Fr bougie. The gastric specimen is removed via the left upper quadrant port site. An endoscopic air leak test is routinely done to confirm an intact staple line, and an upper gastrointestinal contrast study is performed on the first postoperative day before the introduction of oral liquid diet. If this is clear, patients are started on a clear liquid diet and are normally discharged home on post-operative day two with dietary instructions.

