### Evaluation of health care utilization and costs

The impact of bariatric surgery on the health system will be examined by comparing health care use and costs (e.g., physician visits, hospitalizations, medications and associated costs) 3 years pre‐and 2 years post‐surgery (Table 2). In NL, the Centre for Health Information (NLCHI) maintains a number of key health-related data sources on behalf of the provincial Ministry of Health. These databases comprehensively capture patient-specific health care resource utilization. These include vital statistics (mortality) and validated, high quality, detailed measurement of the following health care resources and costs: inpatient and outpatient encounters, physician billings, diagnostic tests, procedures, and long-term care use. In addition to providing detailed information allowing patient-specific costing of each encounter, inpatient databases record diagnostic and procedural information using the ICD-10-CA and CCI classification systems [62]. Using unique provincial health insurance numbers, the NLCHI will link the bariatric clinical/research data with administrative health services data and provide the research team with a de‐identified database of health services use and costs for data analysis purposes [63, 64].

**Table 2 Tab2:** Short to mid-term health care use and costs in surgical patients

Cost Category	Units of Resources	Newfoundland & Labrador Source Details	Newfoundland & Labrador Costing Source	Time Frame
1. Inpatient encounters	# of hospitalizations (acute care) Length-of-stay (LOS)	Newfoundland and Labrador Centre for Health Information (NLCHI) Clinical Database Management System (CDMS), based on the Discharge Abstract Database (DAD) includes LOS, procedures performed, associated diagnoses, RIW and complexity values	NLCHI/Canadian Institute for Health Information (CIHI) methodology to cost acute care encounters using resource-intensity-weights (RIW) and complexity values	Provided by fiscal year. Referenced to time zero (date of surgery)
2. Outpatient encounters	# encounters # procedures	NLCHI CDMS (based on DAD) includes surgical day care procedures	NLCHI/CIHI methodology to cost surgical day care encounters	Provided by fiscal year. Referenced to time zero
3. Physician Fees (Fee for Service)	# of encounters Provider specialty Service provided	Medical Care Plan (MCP) Physician Claims	MCP Physician Claims	Provided by fiscal year. Referenced to time zero

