## Discussion

In summary, the demand for LSG as a stand-alone procedure is growing in popularity as a treatment for class II and III obesity. In a joint report “Developing a Research Agenda to Support Bariatric Care” published by the CIHR and the Canadian Obesity Network in 2010, the gaps in research related to bariatric surgery were highlighted [78]. Although LSG was not specifically highlighted in the report, compared to other bariatric surgeries, research on LSG as a treatment for severe obesity is limited due to its relatively recent provision as a stand-alone procedure. The start-up of a bariatric surgery program offering LSG as a treatment for severe obesity combined with the limited research on LSG provided an opportunity for research. Consequently, an Integrated Knowledge Translation Team was established at Memorial University, comprised of academic researchers, healthcare professionals, decision-makers, and policy makers, and a program of research on bariatric care was developed to address key gaps in the research literature. One of the studies designed and implemented within this program of research and presented in this paper is a quasi-experimental study that aims to address current knowledge gaps in LSG by generating prospective, population-based Canadian outcome data. This study is being conducted in a provincial bariatric surgery program within a tertiary care teaching centre and the results will be generalizable to similar programs offering bariatric surgery. A current review continues to highlight a major concern previously identified by others [79, 80] associated with bariatric surgery as a treatment for obesity. It is not the magnitude of initial weight loss which has been well documented but the mid- to long-term sustainability of weight loss that is under question. Very few bariatric studies report long-term results with sufficient patient follow-up (>80 %) in order to minimize biased results. In addition, insufficient evidence exists regarding long-term outcomes for LSG [61]. In response to this concern and as part of the current study protocol, a clinical database to house all program data in order to monitor longer-term (>5 years) patient health outcomes has been developed which will also allow for data linkages with administrative data to examine health care use and costs in the future. Further interventions being used in order to decrease attrition and increase patient engagement include the use of technology (e.g., Tele-health and webinar sessions for educational purposes). As of August 2015, 100 % recruitment has been achieved with completion of follow-up to be completed by September 2016 with study results to be published in late 2016 and early 2017. Our study population is 82 % female, with an average age, weight, and BMI of 44 years, 135 kgs and 49 kg/m^2^, respectively. The prevalence rates of hypertension and dyslipidemia were approximately 50 and 43 % had T2DM. Our study participants are similar to other patient populations that are eligible for and undergoing bariatric surgery elsewhere in Canada [15, 21], increasing the external validity of our study findings.

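### The planned province-wide linkage is not named as a source for 30-day complications, so events treated outside the programme may be under-counted

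*Protocol article*

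**What the plan says.** In Table 1 (Study measures), the operative-data row gives the source of minor and major complications, from surgery to day 30, as "Clinical database and chart review". The row names no other source. The Discussion describes the study's database as "a clinical database to house all program data in order to monitor longer-term (>5 years) patient health outcomes has been developed".

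Under Setting, the clinic is placed in Eastern Health, one of four regional authorities, and is described as a provincial service. Under Surgical intervention, patients are "normally discharged home on post-operative day two with dietary instructions". Under Data collection, there is a contact with the nurse practitioner or team at 1 month, in person or by Tele-health, and a surgeon assessment at 6–8 weeks.

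The section on health care utilization and costs describes provincial data held by NLCHI: "These include vital statistics (mortality) and validated, high quality, detailed measurement of the following health care resources and costs: inpatient and outpatient encounters", among other items. Inpatient records carry diagnosis and procedure codes. The data are linked to participants by health insurance number, and Table 2 references hospital encounters and physician claims to the date of surgery. The stated product is a de-identified file of service use and costs, and the Secondary outcomes section uses these data only for the economic outcome.

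The Study objective section lists 30-day complications and mortality first and states: "In the short- to mid-term we hypothesize a low rate of complications".

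**The concern.** Discharge on day two leaves about 28 of the 30 days after the patient has gone home, which may be in another authority's area. A leak, bleed or infection treated at a hospital there does not automatically enter a programme database. The source best placed to find it is already part of the study but is assigned to a different outcome.

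Missed events all act in one direction, towards the hypothesised low rate. An admission elsewhere could also enter the cost analysis while being absent from the complication analysis, so the two results could disagree about the same patients. The article itself criticises earlier bariatric studies for bias from incomplete outcome data (Knowledge gaps), so readers will look for complete ascertainment here.

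**Working it through.** The article gives no expected complication rate for this cohort, so there is no plan figure to reproduce. The sample size of 165, inflated to 200, concerns successful weight loss and has no bearing on this point.

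**Routes by which an outside event could be counted**

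- Operative-data row of Table 1: database and chart review. Patient interview and case report form are not listed, although the row on changes in comorbid status lists both.
- 1-month contact and 6–8-week review: an event may be reported and charted. Table 1's form-based follow-up rows start at 3 months, so no item is shown that prompts for outside care at 1 month.
- NLCHI linkage: would show admissions, procedures and deaths anywhere in the province, but is assigned to use and costs.
- Data analysis section: administrative records are among the data entered, without being tied to any outcome.

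**Direction and size**

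Let *p* be the true 30-day rate, *e* the share of events treated outside the programme and *m* the share of those never charted. If no false events are recorded,

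observed rate = *p* × (1 − *e* × *m*).

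The relative understatement is *e* × *m* whatever the value of *p*. It cannot be negative, so missed events can only lower the rate. The documents give neither *e* nor *m*, and no 30-day rate specific to sleeve gastrectomy, so every value below is an assumption.

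With *p* = 10% and 200 patients (20 true events):

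| *e* | *m* | Observed rate | Events counted |
|---|---|---|---|
| 10% | 25% | 10% × (1 − 0.025) = 9.75% | 19.5 |
| 30% | 50% | 10% × (1 − 0.15) = 8.5% | 17 |
| 30% | 100% | 10% × (1 − 0.30) = 7.0% | 14 |
| 50% | 100% | 10% × (1 − 0.50) = 5.0% | 10 |

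The Complications section of the Background cites 4–25% for bariatric surgery in general over the first 30–180 days. Using those ends for *p*, the same extremes of *e* and *m* give 3.9% down to 2.0%, and 24.4% down to 12.5%.

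For scale, the exact 95% confidence interval for 20/200 is 6.2–15.0%, and for 14/200 it is 3.9–11.5%. All but the most extreme row lie inside the first interval. The shift is systematic, however, so a confidence interval around the observed rate does not allow for it.

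**The case against.** A reader might infer that complications come only from the clinic's own records, that events elsewhere are therefore lost, and that the low rate is built in. The text does not go that far.

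- Table 1 does not say that its sources are exclusive and does not confine chart review to Eastern Health charts. Table 2 also uses a similar name, Clinical Database Management System, for an NLCHI source.
- The 1-month contact falls at the end of the window and the surgeon review follows soon after. A serious event treated elsewhere would often come up at one of them.
- The Data analysis section includes administrative records.
- How outside records are obtained is operational detail that an article may leave to the full protocol.

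A reader might also take the 10% under Bariatric surgery outcomes as the expected rate and derive a definite understatement. That figure is pooled over several procedures and carries no 30-day window; only the mortality figure there does. The regional and missed shares are not in the documents at all. Complications are a secondary outcome, and no threshold defines a low rate, so no stated decision turns on the shift.

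Most of this stands. It removes any claim that events are certainly missed, or missed to a known extent. It does not remove the gap: the follow-up contacts depend on the patient's report and on charting, the mention of administrative records is generic, and the passages that assign sources to outcomes leave the linkage out of this one.

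**Conclusion.** The point holds in a limited form. The stated source for 30-day complications does not include the provincial linkage, and events treated outside the programme may be under-counted unless they are reported and charted at the 1-month or 6–8-week contact. The direction of any resulting bias is certain: downward, in line with the hypothesis. Its size cannot be fixed from the documents. The illustrated range, a relative loss of 2.5% to 50%, reflects only the assumed shares. The sample size is unaffected. This is a worthwhile low-cost improvement to a secondary outcome, not a demonstrated error in the plan.

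**What to change.** In Table 1 and in the complications item under Secondary outcomes, add the linked NLCHI inpatient, day-surgery and vital-statistics records as a second source for 30-day death, readmission and reoperation. Count an event found in either source, and report how many came only from the linkage. Keep chart review for minor complications, which administrative codes may capture poorly.

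Recruitment was complete by August 2015, so a prompted question at 1 month is probably too late for most participants. The linkage is retrospective and already planned, so it remains available.

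The cost is extra extraction and coding work. Event dates and code definitions must be requested, because Table 2 describes data supplied by fiscal year, although referenced to surgery. The chart-derived complications need to be in the file sent for linkage. Events can then be counted in the de-identified file. Checking linkage-only events against charts would need re-identification through NLCHI or the research nurse, and the proposal does not depend on it. Some events may be misclassified by administrative codes, and the reported rate may be less favourable.

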### Evaluation of health care utilization and costs

The impact of bariatric surgery on the health system will be examined by comparing health care use and costs (e.g., physician visits, hospitalizations, medications and associated costs) 3 years pre‐and 2 years post‐surgery (Table 2). In NL, the Centre for Health Information (NLCHI) maintains a number of key health-related data sources on behalf of the provincial Ministry of Health. These databases comprehensively capture patient-specific health care resource utilization. These include vital statistics (mortality) and validated, high quality, detailed measurement of the following health care resources and costs: inpatient and outpatient encounters, physician billings, diagnostic tests, procedures, and long-term care use. In addition to providing detailed information allowing patient-specific costing of each encounter, inpatient databases record diagnostic and procedural information using the ICD-10-CA and CCI classification systems [62]. Using unique provincial health insurance numbers, the NLCHI will link the bariatric clinical/research data with administrative health services data and provide the research team with a de‐identified database of health services use and costs for data analysis purposes [63, 64].

**Table 2 Tab2:** Short to mid-term health care use and costs in surgical patients

Cost Category	Units of Resources	Newfoundland & Labrador Source Details	Newfoundland & Labrador Costing Source	Time Frame
1. Inpatient encounters	# of hospitalizations (acute care) Length-of-stay (LOS)	Newfoundland and Labrador Centre for Health Information (NLCHI) Clinical Database Management System (CDMS), based on the Discharge Abstract Database (DAD) includes LOS, procedures performed, associated diagnoses, RIW and complexity values	NLCHI/Canadian Institute for Health Information (CIHI) methodology to cost acute care encounters using resource-intensity-weights (RIW) and complexity values	Provided by fiscal year. Referenced to time zero (date of surgery)
2. Outpatient encounters	# encounters # procedures	NLCHI CDMS (based on DAD) includes surgical day care procedures	NLCHI/CIHI methodology to cost surgical day care encounters	Provided by fiscal year. Referenced to time zero
3. Physician Fees (Fee for Service)	# of encounters Provider specialty Service provided	Medical Care Plan (MCP) Physician Claims	MCP Physician Claims	Provided by fiscal year. Referenced to time zero
4. Physician Fees (self-report)	# of encounters Provider specialty Service provided	Patient interview (standardized case report form)	Estimated using MCP Physician Claims	Information obtained every 6 months
5. Medications	Name dosage, frequency & duration	Patient interview (standardized case report form)	NL Drug (Provincial Formulary)	Information obtained every 6 months
6. Transfer Payments	Unemployment insurance Disability benefits	Patient interview (standardized case report form)	Patient Reported	Information obtained every 6 months
8. Employment status, absenteeism	Employment status in past year (# hours/week, # weeks) Absenteeism in past year (# days) Annual income (by quintile)	Patient interview (standardized case report form)	Average wage rate by age, sex and region from Statistics Canada	Information obtained every 6 months
9. Weight Loss Interventions	Weight loss program, meal replacements, physical trainer, exercise programs, alternative therapies (Binary Y/N)	Patient interview (standardized case report form)	Patient reported out of pocket cost Costs lists of rehabilitation supplies & equipment	Information obtained every 6 months
10. Mobility and Medical	Mobility aids, home modification/renovations, rehabilitation, paid personal assistance (household activities and home productivity, driving) (Binary Y/N)	Patient interview (standardized case report form)	Patient reported out of pocket cost/co-payments for medical services Costs lists of rehabilitation supplies & equipment	Information obtained every 6 months

*DAD* Discharge Abstract Database, *LOS* Length of stay, *CIHI* Canadian Institute for Health Information, *CDMS* Clinical Database Management System, *RIW* Resource Intensity Weight, *MCP* Newfoundland and Labrador Medical Care Plan, *EH* Eastern Health

